
#### Anthropometric Measurements

Anthropometric measurements include body height, body weight, and BMI. Weight is measured using a clinically validated and calibrated scale. Participants must remove heavy clothing (eg, jackets and jumpers) and shoes. Weight is recorded to the nearest 0.1 kg. Height is measured using a calibrated stadiometer. The measurement is taken in an upright position with the feet on a hard surface. The heels, buttocks, shoulders, and the back of the head touch the wall, and the arms are placed at the sides. Height is recorded to the nearest 0.1 cm. BMI is calculated by dividing body weight in kilograms by height in meters squared. Measurements will be taken at 1 month (optional), 3, and 6 months after hospital discharge, each time following the 24-hour dietary recall.

#### Mini Nutritional Assessment Short Form

Screening for malnutrition or risk of malnutrition will be carried out at 1 month (optional), 3, and 6 months after hospital discharge, using the Mini Nutritional Assessment Short Form (MNA-SF). The MNA-SF, consisting of 6 questions, is cost-effective, simple, and suitable for use in hospitals and therefore fulfills the requirements for a screening instrument, which can be used to identify existing malnutrition or the risk of malnutrition in older people [31]. The MNA-SF includes questions on mobility, psychological stress, or acute illness and neuropsychological problems, which increase the risk of malnutrition but do not directly detect malnutrition. The MNA-SF is therefore particularly suitable if the screening aims to detect malnutrition as early as possible [32].

#### Handgrip Strength

There is strong evidence for a correlation between reduced handgrip strength (HGS) and poor nutritional status, increased mortality, complication rates, and hospital length of stay [33-36]. Therefore, HGS will be measured 1 month (optional), 3, and 6 months after hospital discharge, using a dynamometer as follows: participants sitting in a chair with the elbow joint bent 90 degrees. On request, the dynamometer is squeezed as firmly as possible. First, the nondominant hand and then the dominant hand will be tested 3 times each. The highest value for each hand is entered into the database.

#### Refrigerator Door Sensors

The refrigerator at the patient’s home will be equipped with a door sensor recording the opening and closing events of the fridge door. This sensor consists of a small magnet fixed on the door and a sensor with a reed relay attached to the frame. When the door opens or closes, the sensor immediately sends this information to a base unit through an encrypted radio frequency protocol continuously with a resolution of 1 second. The base unit collects the data and sends it to the cloud in real time using the Global System of Mobile Communication networks. The duration of each refrigerator opening is calculated as the time difference between the opening and closing events. The system has been described in detail in the main study, where the sensor system is used to collect digital markers beyond refrigerator openings with the aim of evaluating the system’s potential to detect HF decompensation [27]. The integration of the magnetic refrigerator door sensor into the sensor system to detect refrigerator openings represents a minor extension to the overall setup. The high reliability of the ambient sensor system, with extremely low susceptibility of the sensor and the transmission system, has been shown previously [27]. The refrigerator door sensors will be installed at the patient’s home within 1 week after hospital discharge. Frequency and timing of refrigerator openings are collected over a 6-month period after hospital discharge. The assessment during the study is shown in Figure 1.

**Figure 1 figure1:**
[figure not shown]
Assessments during the substudy.

### Statistical Analysis

We will compute the cross-sectional correlations between protein intake (g) and first refrigerator door opening after midnight in minutes (RDmin) at the start (1 month) and at 3 and 6 months (primary outcome). Further, quantities of interest are the correlation between protein intake (g) and refrigerator opening frequency per day (RDfreq), between energy intake (kcal) and RDmin and RDfreq, between (risk of) malnutrition (score) and RDmin and RDfreq, and between HGS (kg) and RDmin and RDfreq. From the time series of refrigerator opening time after midnight in minutes over the period of 6 months, we will create 3 time windows, each window representing the 2-week period prior to each nutrition assessment (Figure 1). For each window, a mean RDmin measurement will be calculated, resulting in 3 RDmin measurements, 3 RDfreq, and 3 measurements of protein intake (g) and energy intake (kcal) from the 24-hour dietary recalls, 3 measurements of malnutrition and HGS (after 1, 3, and 6 months). We will estimate the cross-sectional associations between RDmin and RDfreq and protein intake (g), energy intake (kcal), (risk of) malnutrition (score), and HGS (kg) at 1, 3, and 6 months to quantify the correlation and to assess the stability of this correlation over time. We will compute Spearman correlation coefficients with corresponding 95% CIs.

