#### Dietary Assessment

For dietary assessment, food intake will be measured using the 24-hour dietary recall. The 24-hour dietary recall is an open-ended, retrospective dietary assessment method. It aims to record as much detailed information as possible about all foods and drinks consumed by the respondent in the previous 24 hours or the day before [28]. In this study, 24-hour dietary recalls are conducted at 3 different timepoints, at 1 month (optional), 3, and 6 months after hospital discharge. The first 24-hour dietary recall at 1 month is optional, as—unlike the assessments at 3 and 6 months—it cannot be coordinated with a routine follow-up hospital visit. Conducting this assessment would require an additional clinic or home visit, which was deemed burdensome for participants. To reduce participant burden and support adherence, this timepoint was made optional. All 24-hour dietary recalls will be conducted on weekdays by trained dietitians in face-to-face interviews. As the main drawback of this method is the forgetfulness of the participants, the 24-hour dietary recalls will be conducted by using the Automated Multiple-Pass Method (AMPM), as described elsewhere [29]. The AMPM uses multiple memory cues with standardized wording to elicit recall of all possible foods. Before the start of the 24-hour dietary recall, it will be recorded whether the day surveyed reflected a usual day in terms of diet or whether it was an unusual day. A usual day is defined as a day on which the participant ate according to their usual habits and routines, reflecting habitual dietary intake. This terminology was chosen to emphasize the importance of capturing habitual intake patterns. Conversely, an unusual day is determined based on the participant’s own judgment and refers to any day they perceive as not representative of their usual intake. Examples will be provided to participants, for example, holidays, celebrations, excursions, acute illness, or other events that may have significantly altered their eating behavior. The amount of consumed food will be estimated using the photo book of the National Nutrition Survey in Switzerland (menuCH) [30] (Multimedia Appendix 1). The conversion of the estimated amounts into weights will follow the menuCH photo book manuals and commercially available packaging sizes in Switzerland. All conversions will be performed by experienced dietitians. Protein intake in grams (g) and energy intake in kilocalories (kcal) will be calculated using nut.s nutritional software (version 1.33.10 - 2022.08.26; dato Denkwerkzeuge) based on the 24-hour dietary recalls. The nutritional database used in nut.s is adapted for the evaluation of Swiss food products.

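### Protein in grams is a valid primary measure, but a prespecified g/kg companion and sex-partial correlations, chiefly for handgrip, would be a cheap improvement

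*Protocol article*

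**What the plan says.** The Statistical Analysis section fixes the unit and the estimator. The primary outcome is set by "We will compute the cross-sectional correlations between protein intake (g") and the time of first refrigerator opening, at 1, 3 and 6 months. The further quantities include the correlation "between HGS (kg) and RDmin and RDfreq". The method is a single sentence: "We will compute Spearman correlation coefficients with corresponding 95% CIs". No scaling to body size, covariate, partial correlation or sex stratum is named.

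The Dietary Assessment section derives the intake in the same absolute unit: "Protein intake in grams (g) and energy intake in kilocalories (kcal) will be calculated using nut.s nutritional software". For grip, the Handgrip Strength section says "The highest value for each hand is entered into the database", with no scaling.

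Weight is available. "Anthropometric measurements include body height, body weight, and BMI", and on timing: "Measurements will be taken at 1 month (optional), 3, and 6 months after hospital discharge, each time following the 24-hour dietary recall". The analysis section gives these values no role. The eligibility criteria do not restrict sex, so men and women can both enter.

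**The concern.** The abstract's objective is an indicator of protein intake. The Discussion and Conclusions go further: they speak of adequate intake and of recognising diets too low in protein, in order to delay sarcopenia and frailty. Whether a given intake is enough depends partly on body size, so 60 g is a different intake at 50 kg than at 100 kg. A correlation with grams does not separate these cases.

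The sex question is separate. If grip strength or protein intake differs between men and women, a pooled coefficient mixes that difference with the association among patients of the same sex. The Introduction itself cites a breakfast and frailty survey whose odds ratio was adjusted for age, sex, body mass index and living alone. Living alone is handled here by eligibility; the analysis section does not mention sex or body size.

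At stake is how the coefficients are read: whether openings say something about adequacy, and whether they say anything within men or within women.

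**Working it through.** The documents give 24 planned patients, 12 recruited by June 2025, and no formal power calculation. There is therefore no stated figure to reproduce. They give no standard deviations, sex mix or sex differences, so every such input below is an assumption.

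**1. Unit of protein, if openings track g/kg.** Take grams = (g/kg) × weight, both log-normal, with weight independent of g/kg and of opening time. With s = √ln(1+CV²), the log-scale correlation with grams equals the correlation with g/kg times s(g/kg) / √[s(g/kg)² + s(weight)²].

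For CVs of 25% (g/kg) and 20% (weight), s = 0.246 and 0.198, and the factor is 0.246/√(0.0606+0.0392) = 0.78. Simulation with 200,000 draws and a log-scale correlation of -0.40 gave these Spearman values:

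| CV g/kg | CV weight | with g/kg | with grams | factor |
|---|---|---|---|---|
| 25% | 15% | -0.386 | -0.328 | 0.855 |
| 25% | 20% | -0.382 | -0.296 | 0.779 |
| 25% | 25% | -0.387 | -0.273 | 0.707 |
| 35% | 20% | -0.387 | -0.334 | 0.864 |
| 45% | 15% | -0.380 | -0.359 | 0.945 |
| 45% | 25% | -0.383 | -0.332 | 0.868 |

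The loss runs from about 5% (1 - 0.945) to 29% (1 - 0.707).

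**2. The mirror case.** Let openings track grams, with weight independent of grams and of opening time. The formula is the same with the roles exchanged. With a CV of 25% for grams and 20% for weight, the correlation is -0.38 with grams and -0.38 × 0.78 = -0.30 with g/kg.

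**3. Sex, when unrelated to opening time.** Let the outcome differ by d within-sex SDs between men and women, with a share p of one sex. The pooled SD is √[1 + p(1-p)d²], so the within-sex correlation is multiplied by its inverse.
- d = 2.0, 50:50 mix: 1/√(1 + 0.25×4) = 0.71
- d = 2.0, 70:30 mix: 1/√(1 + 0.21×4) = 0.74
- d = 0.8, 50:50 mix: 1/√(1 + 0.25×0.64) = 0.93

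**4. Sex, when related to opening time.** Assume no within-sex association, a 50:50 mix and n=24. The last two columns are two-sided 5% rejection rates from 4,000 simulated trials. They correspond roughly to how often a 95% CI would exclude zero.

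| Sex difference in opening time (SD) | Sex difference in outcome (SD) | pooled Spearman (large sample) | crude | sex-partial |
|---|---|---|---|---|
| 0 | 2.0 | 0.00 | 6.0% | 5.1% |
| 0.5 | 0.8 | 0.09 | 6.3% | 4.8% |
| 0.8 | 0.8 | 0.14 | 10.1% | 5.1% |
| 0.5 | 2.0 | 0.18 | 13.3% | 4.7% |
| 0.8 | 2.0 | 0.27 | 26.4% | 5.5% |

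**5. Cost of adjustment.** Use Fisher's z with the Bonett-Wright variance (1 + r²/2)/(n-3-k), where k is the number of covariates. The correlation detectable with 80% power is tanh[(1.96+0.84) × √(1.06/(n-3-k))], taking 1.06 as the numerator.
- n=24: 0.56 (k=0), 0.57 (k=1), 0.58 (k=2)
- n=12: 0.745 (k=0), 0.797 (k=2)

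The 95% CI around -0.3 at n=24 goes from (-0.63, 0.13) with k=0 to (-0.65, 0.15) with k=2.

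**The case against.** The strongest reply is that nothing here is an error. The objective is an indicator of protein intake, and grams is its direct unit. The one protein threshold that the article cites, 30 g at two or more meals, is absolute, and no per-kg target appears. This stands, and it is why grams should remain primary. A reader might infer that the primary unit is wrong and must be replaced by g/kg. The documents do not support that: adequacy is a downstream hope, and weight in patients admitted for decompensation and treated with diuretics partly reflects fluid.

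A reader might also infer that the primary correlation is diluted by roughly a quarter. That holds only if openings track g/kg. Step 2 gives the same loss the other way round, and the documents favour neither case. Wider intake variation, plausible for a single-day recall, shrinks the loss further. Sampling error is also far larger: at n=24 the 95% CI is -0.69 to 0.04 around -0.38 and -0.63 to 0.14 around -0.29.

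That sex confounds the result is likewise not shown, because nothing links sex to opening pattern. A crude coefficient is legitimate as description in a pilot. It cannot, however, show that openings carry information within men or within women.

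Finally, companion scalings and adjusted analyses are often left to an analysis plan, which is not shown. The point therefore rests on what the article does fix, the units and the plain estimator, and not on an omission.

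**Conclusion.** This is a cheap improvement to consider, not a defect in the primary outcome. Correlating openings with grams is sound for total intake but is silent on adequacy for body size. The price of the wrong scale is about 5% to 29% of the correlation under CVs of 25% to 45% for intake and 15% to 25% for weight, and it can fall on either scale. Showing both is more informative than relying on one.

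The sex point is clearest for handgrip. Even if sex is unrelated to opening time, pooling multiplies a within-sex correlation by about 0.71 for an assumed 2 SD difference at 50:50. If sex also shifts opening time by an assumed 0.5 to 0.8 SD, the crude false-positive rate at n=24 is about 13% to 26%. For a 0.8 SD outcome difference, used here for protein, the effects are smaller: a factor of 0.93 and a rate of about 6% to 10%. All sex differences and the sex mix are assumptions.

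**What to change.** Keep protein in grams as the primary measure. Before the analysis starts, prespecify two additions:
- protein in g per kg of the body weight measured at the same visit, as a companion correlation;
- sex-partial Spearman coefficients with 95% CIs beside the crude ones, for handgrip and for protein, with the sex mix reported.

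No new measurement of weight is needed. Sex is assumed to be among the baseline parameters that the article refers to the main-study protocol. Adjustment costs about one degree of freedom per covariate, which is small at 24 patients but more noticeable if numbers stay near 12. The g/kg result carries fluid-related error in its denominator, so it should be read beside grams and not in place of it.

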**Objective:**

The aim of this study is to determine whether the time of the first refrigerator opening in the morning can serve as a potential indicator of protein intake in older patients (age ≥70 years) after hospitalization for HF decompensation over a period of 6 months.

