**Methods:**

This is a substudy of a prospective interventional cohort study that aims to identify changes in digital biomarkers derived from an ambient sensor system, which may support the early detection of HF decompensation. In this substudy, the frequency and timing of refrigerator door openings in participants’ homes will be measured. To assess associations between protein intake and refrigerator openings, dietary intake will be evaluated using 24-hour dietary recalls at 3 different timepoints: at 1, 3, and 6 months after hospital discharge. All 24-hour dietary recalls will be conducted by trained dietitians in face-to-face interviews on weekdays. The primary outcome of this study will be the correlation between protein intake and the time (in minutes after midnight) of the first refrigerator door opening at each of the 3 assessment points.

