The use of refrigerator openings (eg, the first door opening of the day or frequency) as indicators for increased risk of sarcopenia and frailty would provide an easy monitoring opportunity. In this context, the study by Schütz et al has shown that the time of the first refrigerator opening in the morning indicated by a door sensor at the refrigerator may correlate with frailty in older single living persons [19]. Notably, approximately one-third of older people in Switzerland live alone [23], emphasizing the relevance of such monitoring approaches. Prior studies have also shown that living alone increases the odds of falling among community-dwelling older adults [24-26]. With such simple assessment tools, interventions could be initiated at an early stage to reduce the risk of these diseases. This, in turn, would have a positive impact on the quality of life of those affected and could also help to reduce health care costs.

As a part of prospective interventional cohort study (for details refer to study protocol of Vögeli et al [27]), a substudy will be conducted with the aim of evaluating the sensitivity and specificity of the time of the first refrigerator opening in the morning as a potential indicator for protein intake in older patients after hospitalization for HF decompensation over a period of 6 months.

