## Methods

### Study Design and Participants

In this prospective cohort pilot study, 24 consecutive patients living alone at their homes who were hospitalized for HF decompensation at 2 secondary care hospitals (Solothurner Spitäler AG) in Olten and Solothurn, Switzerland, will be included.

The inclusion criteria are current hospitalization for HF decompensation, age≥70 years, left ventricular ejection fraction <50% and treatment with diuretics, New York Heart Association class II or III, living alone, willingness to participate with informed consent, and agreement to attend follow-up visits at the hospital at 3 and 6 months. Exclusion criteria include major depression (9-item Patient Health Questionnaire [PHQ-9] score >9) or being on hemodialysis. In addition, patients with a left ventricular assist device, or those who had undergone coronary revascularization or cardiac resynchronization therapy implantation within 28 days before the index event of HF decompensation, or have been scheduled for such interventions, are excluded from the study.

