## Discussion

### What Does the Study Offer?

Because overall diet quality is associated with the risk of frailty, and insufficient protein intake leads to loss of muscle mass and strength [13,14], more attention should be paid to healthy nutrition and adequate protein intake in patients with HF. Although results from other studies suggest that patients with HF may benefit from a high-protein diet, conclusive evidence from prospective controlled clinical trials, particularly in relation to mortality, is scarce. Individual studies, such as a randomized double-blind pilot study in 29 patients with HF, have shown improvements in quality of life after 18 weeks on a high-calorie, high-protein diet [37]. However, most studies on protein intake are observational and have been conducted in the general population [38], while limited data are available for patients with HF. Simpler and more innovative tools for collecting information on protein intake in patients with HF could reduce the burden of long-term home monitoring. Furthermore, such tools may help minimize recall bias, which is particularly problematic in older adults when using retrospective dietary assessment methods. Refrigerator openings could represent such a tool, both in terms of the first opening of the day and overall frequency. For example, a late first refrigerator opening after midnight may be indicative of skipping breakfast. In general, little is known about the nutritional status of older people who skip breakfast, and there are contradictory results regarding meal frequency and frailty [39,40].

To the best of our knowledge, this is the first prospective study investigating the use of refrigerator openings as a potential indicator of protein intake. The use of the refrigerator openings in relation to frailty and sarcopenia would allow easy monitoring. Interventions could be initiated at an early stage and thereby reduce disease progression.

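### RDmin is worded as the first opening after midnight, with no start time for the morning, so a night-time opening can replace the morning opening that the objective names.

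*Protocol article*

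**What the plan says.** The Abstract objective is to find out "whether the time of the first refrigerator opening in the morning can serve as a potential indicator of protein intake". The end of the Introduction names the same event when it speaks of the "sensitivity and specificity of the time of the first refrigerator opening in the morning as a potential indicator for protein intake". In both places the quantity of interest is a morning event.

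The Abstract methods give the primary outcome as "the correlation between protein intake and the time (in minutes after midnight) of the first refrigerator door opening" at each assessment. The Statistical Analysis section words the variable as "first refrigerator door opening after midnight in minutes (RDmin" and reduces the daily values to one number per window: "For each window, a mean RDmin measurement will be calculated", with "each window representing the 2-week period prior to each nutrition assessment". Spearman coefficients with 95% CIs are then computed on those window means.

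The Discussion (What Does the Study Offer?) gives the intended meaning: "a late first refrigerator opening after midnight may be indicative of skipping breakfast".

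The Refrigerator Door Sensors section says that openings and closings are recorded continuously at 1-second resolution. Night openings are therefore in the data. No section says at what hour the morning starts or how a night opening is treated.

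**The concern.** The event in the objective and the event in the analysis variable are not the same. An analyst who follows the Statistical Analysis wording starts the clock at 00:00. If a participant opens the refrigerator at 01:00 and again at 07:30, that day's RDmin is 60 and not 450. A participant who opens it at night and then skips breakfast is scored as an early opener, which is the opposite of the Discussion's interpretation.

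The window mean passes each such night on in full proportion. Spearman's coefficient does not repair this, because it ranks patients after the within-patient mean has been taken.

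At stake is the primary outcome. If night openings are common and uneven between patients, a weak correlation could mean that breakfast time does not track protein intake, or only that the variable mixed night waking with breakfast time. The results could not tell these apart.

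**Working it through.** The plan has no figure of its own to reproduce: the sample size of 24 comes without a power calculation, and no distribution of opening times is given. From the documents come n = 24, a 2-week (14-day) window, the arithmetic mean and the Spearman coefficient. All clock times, SDs and night-opening rates below are assumptions.

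**1. Shift of one patient's mean.** Let m be the usual morning opening in minutes after midnight, t the time of a night opening, and k the number of affected nights out of 14.

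Window mean = ((14 - k)m + kt)/14 = m - k(m - t)/14

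With m = 450 (07:30) and t = 60 (01:00), the shift per affected night is 390/14 = 27.9 min:

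| k | shift (min) | window mean (min) |
|---|---|---|
| 1 | -27.9 | 422.1 |
| 2 | -55.7 | 394.3 |
| 3 | -83.6 | 366.4 |
| 5 | -139.3 | 310.7 |

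With t = 120 (02:00) the shift is 330/14 = 23.6 min per night. For morning times from 07:00 to 08:00 and night openings from 01:00 to 03:00, three affected nights move the mean by 51 to 90 min.

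**2. Why ranks are affected.** Patient A always opens first at 07:30, so the mean is 450. Patient B has a usual morning opening at 08:30 (510) and opens at 01:00 on three nights, so the mean is 510 - 3(510 - 60)/14 = 510 - 96.4 = 413.6, about 06:54. B is the later morning opener but ranks as the earlier one.

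**3. Effect on the correlation (simulation).** The set-up is 24 patients, 14 days, latent correlation -0.5 between usual morning time and protein intake, mean morning time 07:30 and day-to-day SD 45 min. Night openings fall uniformly between 00:00 and 05:00. Each patient's night-opening probability is drawn from a beta(1, 1/p - 1) distribution with mean p. There are 1000 replicates per row. Mean Spearman coefficients are:

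| between-patient SD (min) | p | morning opening, mean | from midnight, mean | from midnight, median |
|---|---|---|---|---|
| 45 | 5% | -0.44 | -0.39 | -0.43 |
| 45 | 10% | -0.46 | -0.35 | -0.43 |
| 45 | 20% | -0.44 | -0.24 | -0.33 |
| 60 | 5% | -0.45 | -0.42 | -0.45 |
| 60 | 10% | -0.46 | -0.39 | -0.44 |
| 60 | 20% | -0.46 | -0.30 | -0.36 |
| 90 | 5% | -0.46 | -0.44 | -0.45 |
| 90 | 10% | -0.46 | -0.41 | -0.44 |
| 90 | 20% | -0.47 | -0.35 | -0.38 |

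A second run used between-patient SD 60 min and night times from 00:00 to 04:00. The coefficient fell from about -0.45 to -0.40, -0.35 and -0.28 at 5%, 10% and 20% of nights.

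**4. Two variations on the assumptions.** If every patient has the same night-opening probability, the coefficient falls only from about -0.46 to -0.43, -0.41 and -0.37 at 5%, 10% and 20%. If later morning openers also open more at night (assumed link 0.5), it is about -0.18 at 20% and -0.06 at 30%. The mean coefficient does not change sign in any of these settings.

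**The case against.** The strongest reply is that minutes after midnight is only the unit. The Abstract methods put the phrase in brackets after the word time, and the abbreviation list defines RDmin without the word first. The objective and the Introduction consistently say morning. Read together, morning could be the event and midnight the zero of the scale. This reading is possible, and it means that the document does not prove that night openings will be used. But the Statistical Analysis section and the Discussion both attach midnight to the first opening itself, and no text supplies a start for the morning under either reading.

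A second reply is that an article may leave the start hour to the full protocol or SAP. That would hold if the variable had been left open. Here a definition is stated, and taken literally it measures something other than the objective.

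A third reply is that the size is assumed. This stands. A shift common to all patients leaves Spearman's coefficient unchanged, so only differences between patients matter. At 5% of nights the loss is small. The sampling SD of the coefficient at n = 24 is about 0.17, so the bias at 5 to 10% of nights is below sampling noise, though it does not average out. The simulated morning rule also looks perfect by construction, because no simulated night opening falls after the cut-off.

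A reader might go further in three ways that the documents do not support:

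- **Diuretic use shows that night openings are frequent.** The eligibility criteria do require "left ventricular ejection fraction <50% and treatment with diuretics" and age of at least 70 years. Nothing is said about night rising or about opening the refrigerator then. It is a plausible inference only.
- **The correlation would be reversed.** The calculations show attenuation; a reversal applies only to the ranks of individual patients.
- **A day at home with no opening drops out of the mean.** No section states a rule for such days, so none can be criticised.

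**Conclusion.** The concern holds as a mismatch between the objective and the wording of the primary variable. Followed literally, RDmin lets a night opening replace the morning opening, and neither the window mean nor the later ranking undoes it. The shift of about 28 min per affected night is plain arithmetic, given an opening at 01:00 and a usual opening at 07:30. The effect on the primary correlation depends on how often night openings occur and how much they differ between patients, and the documents give neither. On the assumed inputs it is small at about 5% of nights and material at about 10 to 20%. A median over the window recovers most of the loss at 10% of nights but not at 20%, so the missing morning start is the core of the problem and not the choice of mean. The Limitations section mentions great variation in opening patterns but does not deal with this. The study is a pilot and the remedy is nearly free, so the point is a cheap improvement and not a flaw that invalidates the study.

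**What to change.** Before analysis starts, state that RDmin is the first opening at or after a prespecified morning start time, still expressed in minutes after midnight. Alternatively, use the first opening after the main sleep period, if the ambient system records it; the Introduction says that such systems can monitor sleep. A start such as 04:00 or 05:00 is only an example. What matters is that it is fixed before the data are analysed.

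Keep the from-midnight version as a sensitivity analysis and report night openings as a separate count, so that readers can see how common they are. The window median can be added as a robustness check, but it does not replace the morning start.

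The cost is one sentence and a few lines of code. The time stamps are already collected at 1-second resolution, and the Results section says that analysis begins only after all data are collected. The downside is that a rare true breakfast before the chosen start would be missed.
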